#### Methods for additional analyses (e.g. subgroup analyses) {20b}

Subgroup analyses will be performed for age, gender, time of medication, maximum duloxetine dosage and average weekly pain score. Multiple logistic regression will be used to evaluate and determine the interference of the above confounding factors in the primary outcome. All analyses will be performed using both the intention-to-treat and per-protocol principles, and the final conclusion will be in line with the intention-to-treat principle.

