**Methods:**

This is a nationwide multicentric, randomized, open-label, blinded-endpoint study that will recruit 750 participants from 18 primary centres in China. Patients aged more than 50 years who are diagnosed with uncomplicated HZ, present with vesicles within 72 h of their emergence, and have an average pain score of at least 40/100 mm on a visual analogue scale (VAS, 0 mm = no pain, 100 mm = worst possible pain, at opposite ends of a 100-mm line) will be recruited for this study. Participants will be randomized into a duloxetine arm and a control arm. Participants allocated to the duloxetine arm will be given antivirals, analgesics and duloxetine, while those allocated to the control arm will receive antivirals and analgesics but no duloxetine. The primary outcome of this study is preventive efficacy against PHN, which will be evaluated based on a 100 mm VAS. Any pain scores other than 0 mm on the VAS 12 weeks after HZ onset will be defined as PHN. The secondary outcomes will consist of the average weekly VAS score, the average weekly consumption of each analgesic, weekly feature of the pain, patients’ quality of life based on the 12-item Short-Form Health Survey, Patient Global Impression of Change Scale, sleep quality as evaluated by the Pittsburgh Sleep Quality Index and adverse events during the study period.

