### Intervention description {11a}

For participants assigned to the duloxetine arm, 20 mg duloxetine (YouBiLuo®, NHWA, China) will be orally administered once daily, after breakfast. If the patient’s VAS score reaches 0 within the first week, duloxetine will be discontinued; otherwise, it will be increased to 40 mg once daily, for the second week. If the VAS score reaches 0 within the second week, duloxetine will be tapered down to 20 mg once daily for a week and discontinued; otherwise, it will be increased to 60 mg once daily and maintained until a VAS score of 0 is obtained, or until the end of the 10th week. Then, duloxetine will be tapered to 40 mg once daily for a week, followed by 20 mg once daily for a week, and then discontinued. For participants who develop adverse effects, the dose will be adjusted to the last tolerated level. Participants in the control arm will not be given duloxetine during the 12-week treatment period.

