### Statistical methods

#### Statistical methods for primary and secondary outcomes {20a}

Statistical analyses will be performed using the SPSS 25.0 software package for Windows (SPSS, Inc., Chicago, IL, USA). The baseline and outcomes for the intervention will be compared to the control arm for primary analysis. Continuous variables will be expressed as the mean (SD) or median (IQR) and compared using Student’s *t* test or the Mann-Whitney *U* test. Normality will be tested using the Kolmogorov-Smirnov test. Categorical variables will be expressed as the number of patients (percentage) and compared using the chi-squared test or Fisher’s exact test. A 2-tailed alpha of 0.05 will be used as the threshold of statistical significance. The incidence of PHN in each arm at the end of week 12 will be compared using the chi-squared test. Subgroup analyses will be performed for age, gender, time to medication, maximum duloxetine dosage and average weekly pain score. Multiple logistic regression will be used to evaluate and determine the interference of the above confounding factors in the primary outcome. All analyses will be performed using both the intention-to-treat and per-protocol principles, and the final conclusion will be determined in line with the intention-to-treat principle.

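### Maximum duloxetine dose and average weekly pain score arise after randomisation and should not be used as subgroup factors or as confounders in the logistic regression on PHN

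*Protocol article*

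**What the plan says.** The list of factors appears twice. The section on additional analyses {20b} says "Subgroup analyses will be performed for age, gender, time of medication, maximum duloxetine dosage and average weekly pain score". The main statistical section {20a} says "Subgroup analyses will be performed for age, gender, time to medication, maximum duloxetine dosage and average weekly pain score", and continues: "Multiple logistic regression will be used to evaluate and determine the interference of the above confounding factors in the primary outcome". The list thus serves both for subgroups and as the covariates of the regression on the primary outcome.

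Other sections show what two of the five variables are.

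- **Maximum dose.** Under Intervention description {11a}, the first step depends on whether the "VAS score reaches 0 within the first week, duloxetine will be discontinued; otherwise, it will be increased to 40 mg once daily". The second step reads: "otherwise, it will be increased to 60 mg once daily and maintained until a VAS score of 0 is obtained". Tolerability also enters: "For participants who develop adverse effects, the dose will be adjusted to the last tolerated level". For the other arm, "Participants in the control arm will not be given duloxetine during the 12-week treatment period".
- **Average weekly pain score.** The abstract names the "average weekly VAS score" among the secondary outcomes, and the list under Secondary outcomes repeats it. It comes from the daily diary kept after recruitment. The Primary outcomes section defines PHN as any non-zero reading on the same VAS at 12 weeks.

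Section {20a} makes the primary comparison a chi-squared test of PHN incidence at week 12. Both {20a} and {20b} tie the final conclusion to intention-to-treat.

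**The concern.** A confounder in a treatment comparison must precede treatment. Randomisation already deals with such variables on average, so adjustment is useful only for baseline factors. Neither variable qualifies.

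Weekly pain lies on the path from treatment to PHN and is close to the endpoint itself. Holding it fixed blocks part of the effect that the trial is designed to measure.

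Maximum dose records three things together: arm, failure to reach zero pain early, and tolerability. A dose stratum of 20, 40 or 60 mg contains only duloxetine patients, so it offers no randomised comparison. The 60 mg group is enriched by design with people whose pain persisted.

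At stake is the reading of the secondary results. This regression is the only adjusted analysis of PHN that the article describes. The Discussion says the trial does not address the optimal dose, yet a table of PHN by dose reached would invite that reading.

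**Working it through.** The plan gives no figure for these analyses, so the check takes its design rates and asks what the listed variables do to them.

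**Inputs from the protocol.** PHN 30% (control) and 20% (duloxetine), from Sample size {14}; 1:1 allocation; the dose steps in {11a}; PHN defined as VAS above 0 at week 12.

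**Assumptions not in the protocol.** Twelve weekly VAS values starting from a mean near 55 mm and declining linearly, truncated at 0 and 100. Between-patient SD 15 to 22 mm, within-patient SD 10 to 25 mm. Either 0% or 15% of patients capped at 20 or 40 mg for adverse effects. The decline is calibrated to the design rates. There were 300,000 simulated patients per scenario, so sampling error is small and the uncertainty lies in the assumptions.

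**Step 1: the target.** The design rates imply OR = (0.20/0.80) / (0.30/0.70) = 0.250/0.4286 = 0.583 and a risk difference of -10 points. The unadjusted simulated ORs were 0.57 to 0.59.

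**Step 2: add average weekly pain, true effect present.** The arm OR moved to 0.69-0.80. The risk difference, standardised over weekly pain, shrank from about -10 points to between -2.6 and -3.6. With an inert drug the arm OR stayed near 1.0, so the distortion here is attenuation. A separate model, in which the drug shortens the time to zero pain and VAS falls smoothly to zero, gave 0.58 moving to 0.66. Taken together: roughly 0.66-0.80.

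**Step 3: PHN by dose reached, inert drug, 15% capped.**

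| SD between / within (mm) | 20 mg | 40 mg | 60 mg |
|---|---|---|---|
| 22 / 10 | 23.4% | 24.7% | 31.5% |
| 22 / 20 | 19.8% | 21.0% | 33.2% |
| 15 / 25 | 23.8% | 24.6% | 32.0% |

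The drug does nothing in these runs. The gradient comes from the titration rule.

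**Step 4: add numeric dose to arm, same runs.** The arm ORs were 0.54, 0.34 and 0.53, where the truth is 1.0. The ORs per 20 mg were 1.26, 1.50 and 1.27.

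The reason is algebraic. Controls all sit at dose 0, so the arm term describes a treated patient at 0 mg, who does not exist. It must offset the dose slope at the mean dose. In the first scenario the shares at 20, 40 and 60 mg were 0.093, 0.093 and 0.814. The mean dose in 20 mg units is 0.093×1 + 0.093×2 + 0.814×3 = 2.721. Then exp(-2.721 × ln 1.258) = exp(-0.624) = 0.54, which is the fitted value. The second scenario gives exp(-2.641 × ln 1.497) = 0.34.

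Without capping, the arm OR was 0.15 or lower, or the model failed to converge because hardly any low-dose patient had PHN.

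**Step 5: dose as a category.** With levels 0, 20, 40 and 60 mg, dose 0 is the control arm exactly. Arm and dose are then linearly dependent, and the arm effect cannot be estimated.

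**The case against.** The strongest reply is that nothing decisive rests on these analyses. The primary test is unadjusted and the conclusion follows intention-to-treat. That stands, and it limits the point to the subgroup and regression results.

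Second, the article never says that arm is a term in the regression. A reader might infer that the trial's adjusted treatment effect will be wrong, but the text does not state such an estimate. What can be said is conditional: if arm is included, its coefficient loses its meaning; if it is not, an outcome and an arm-defined dose are still labelled confounders. The subgroup problem remains either way.

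Third, several stronger readings are tempting but not supported:

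- *That adjusting for weekly pain removes the treatment effect.* The models in Steps 1 and 2 show attenuation, and its size depends on assumed variances. Other assumed trajectories gave ORs of 0.74 to 0.98, so 0.66-0.80 is not a bound.
- *That a real benefit would necessarily be reported as no effect.* Weekly pain pulls the OR towards 1, whereas numeric dose can create a false benefit. With both in the model, the arm OR under a true benefit ranged from about 0.7 to above 10, or the fit failed. The direction cannot be predicted.
- *That low-dose patients would have no PHN and the 60 mg group all of it.* This needs pain that falls to zero without fluctuation and no dose reduction for adverse effects. The protocol provides for such reductions.
- *That the arm effect is never identifiable.* This holds only for categorical dose, and the plan fixes no coding.

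Time to medication need not be redefined for the control arm's sake, because all participants receive valacyclovir.

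**Conclusion.** The point holds for two of the five listed variables. It is a stated choice, made in both statistical sections, and not a detail left to an analysis plan. The protocol's own text shows that both variables are determined after randomisation.

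The absence of controls from every dose stratum, the selection of persistent pain into 60 mg, and the non-identifiability with categorical dose follow from the protocol without simulation. The sizes in the working are illustrative: they depend on assumed VAS variances and, for the dose results, on an assumed 15% of patients being capped. The attenuation, the dose gradient and the false arm benefit under an inert drug each kept their direction in every tabulated or capped scenario.

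The primary chi-squared intention-to-treat comparison and the final conclusion are unaffected. This should be corrected before analysis, but it does not put the main result in doubt. If baseline pain was what was meant by average weekly pain score, the text has to say so; as written it matches the secondary outcome.

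**What to change.** In both {20a} and {20b}:

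1. Delete maximum duloxetine dosage and average weekly pain score from the subgroup list and therefore from the regression.
2. Use baseline VAS as the pain variable. It is already collected, since eligibility requires at least 40/100 mm.
3. State that the regression of week-12 PHN contains arm and baseline factors only, and do not call those factors confounders.
4. Report the dose reached descriptively, in the duloxetine arm only, with no comparison of PHN between dose levels presented as a dose effect.

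Average weekly VAS remains a secondary outcome, compared between arms as planned.

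The cost is a wording change: no new data, no change in sample size and no change to any dosing rule. One point for reporting: an OR adjusted for baseline pain is on a conditional scale and can differ from the unadjusted OR without bias. In one scenario it was 0.36 against 0.58 under the design effect, and 1.00 for both under no effect. Presenting the unadjusted risk difference beside it avoids misreading.

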#### Methods in analysis to handle protocol non-adherence and any statistical methods to handle missing data {20c}

At least two research assistants from each centre will be trained in detail regarding the same protocol, before the implementation of this study. The research assistants will be readily available to answer any questions throughout the entire study period of 12 weeks, and monitor the participants’ completion of the PDs and deliver reminders as necessary through telephone calls or social media. PD recordings are mandatory and missing data are not to be expected. All outcomes will be analysed according to the intention-to-treat principle, and once enrolled, all patient data will be analysed irrespective of the findings.

#### Plans to give access to the full protocol, participant-level data and statistical code {31c}

Patient information will be kept confidential and only the lead investigator of each centre will have access to the files corresponding to the personal data of the respective participants. After completion of the study, the results will be made public through publication in a scientific journal along with conferences related to pain management, and the clinicaltrials.gov website. Necessary data will also be considered to be made available from the corresponding author on reasonable request.

### Oversight and monitoring

#### Composition of the coordinating centre and trial steering committee {5d}

The coordinating centre (CC) will be responsible for the training of all research assistants and the coordination of all standardized quality control aspects such as PDs, operation manual and forms. It will include a Principal Investigator (PI), two expert pain management specialists, a pain management nurse and a statistician. It will serve as a link between all the 18 centres involved in the study, the research assistants involved in recruitment, assistance and follow-up.

The trial steering committee (TSC) will include the PI, an independent chair, two independent pain physicians and an independent statistician. It will supervise the trial progress, resolve unanticipated complications if any and assess AE and SAE and their potential correlation with the study drugs. It will supervise the work of various subcommittees such as quality control subcommittee for the training of research assistants, subcommittee of research assistants involved in recruitment and clinical activities, subcommittee for publications and presentations at the completion of the study. The TSC will report any unforeseen events and report to the IRB. The IRB of Beijing Tiantan Hospital will be supervising the trial and meet at least annually to oversee the study conduct and progress.

#### Composition of the data monitoring committee, its role and reporting structure {21a}

The data monitoring committee (DMC) comprised of two statisticians and a pain physician will perform independent review of data outcomes and patient safety. It will meet biannually and report to the TSC.

#### Adverse event reporting and harms {22}

The TSC will conduct regular inspections of the trial progress and report any unforeseen events to the IRB. Any AE or SAE (serious adverse events) will be reported to the IRB (Institutional Review Board) for judgement. Anticipated severe problems that may be detrimental to the participants involve rapid-onset hyponatremia, delirium and haemodynamic instability. Such serious life-threatening adverse events as well as other severe complications leading to prolonged hospital stay or death will be reported to the IRB and our study will be terminated immediately.

#### Frequency and plans for auditing trial conduct {23}

The IRB will be making regular inspections of trial conduct. The progress report of this PROCESS trial will be submitted to the IRB 1 month ahead of the date, 2020/12/31, and will be reviewed annually.

#### Plans for communicating important protocol amendments to relevant parties (e.g. trial participants, ethical committees) {25}

Any deviations from the protocol will be fully documented in a breach report form, recorded in a protocol deviation log and reported to all relevant parties. Although protocol modifications are not to be expected, any modifications due to unforeseen circumstances will be reported to the regulatory bodies by sending updated versions of the protocol. A copy of the revised version will be stored by the PI and updated in the clinical trials registry website.

#### Dissemination plans {31a}

After completion of the study, the results will be made public through publication in a scientific journal along with conferences related to pain management, and the clinicaltrials.gov website.

## Discussion

This is a large randomized, multicentric, open-label, blinded-endpoint study aiming to test whether premedication with duloxetine within 72 h after VZV reactivation has a preventive effect against PHN. To the best of our knowledge, this study is the first to examine the preventive effects of duloxetine on PHN. PHN is the most common complication following acute HZ. Based on recent epidemiological studies, 61.8% to more than 70% of PHN cases in China develop in patients aged more than 50 years [3, 4]. The results of these studies were consistent with previous findings in western countries [6]. Patients older than 50 years have long been the main subjects for studies on PHN in prior clinical trials [19, 21]. For a pragmatic study design, only patients aged more than 50 years will be included in the present study. Duloxetine, a serotonin–norepinephrine reuptake inhibitor, was first approved for primary depression. In recent years, it has also been recommended as the first-line [24] therapy for neuropathic pain. The recommended usage of oral duloxetine is to start at 30 mg once a day and gradually increase by 30 mg each time until the optimal dosage. An alternative usage is to begin at 20 mg and increase by 20 mg each time until optimal dosage. In this study, the latter is chosen for its superior accuracy. The maximum dosage of duloxetine allowed is 120 mg per day. In the treatment of diabetic neuropathy and fibromyalgia, a higher dosage of duloxetine demonstrated no benefit compared to 60 mg per day and was not tolerated as well as the lower dose. On the other hand, pharmacodynamically, duloxetine inhibits the uptake of both serotonin and norepinephrine, of which the former is inhibited much more strongly than the latter. One study suggests that the inhibition of norepinephrine (NE) [31] is relatively weak if the daily oral dose of duloxetine is less than 60 mg. In our study, patients aged more than 50 years will be recruited. Hence, considering the safety issues and pharmacodynamic effectiveness, 60 mg per day will be set as the maximum dosage. Long-term tolerance has been proven by a previous study, in which duloxetine was administered at 60 mg twice per day for 52 [32] consecutive weeks. No severe drug-related side effects or AEs were observed. Notably, duloxetine was found with rapid-onset hyponatremia and delirium, according to a recent investigation [33]. Concerning events will be carefully monitored throughout the study period. Regarding drug interactions, duloxetine is not documented to be a contraindication to valacyclovir or vice versa. Similarly, based on our pilot study, no specific adverse events were observed for duloxetine in combination with valacyclovir, and no drug interactions were detected. During the study period, the principal investigators will monitor all AEs and SAEs in real time. The safety precautions in our study will be further adjusted based on the study process and AE reports.

This study has several limitations. An open-label design instead of a blinded, placebo-controlled design will be used in this nationwide multicentric study due to limited funding support. Although an open-label trial [34] reflects real clinical circumstances more effectively than a blinded trial and maintains the advantages of randomized allocation and blinded outcome assessors, the therapy recommended for the control arm can be considered an active control, as the intervention of duloxetine involves an add-on therapy, the effect of placebo may not be well perceived. As a result, VAS in the duloxetine arm may be underestimated; however, limited impact on primary outcome is assumed as any pain score other than 0 on the VAS at 12 weeks after HZ onset will be established as PHN. Although lower VAS is expected for the duloxetine arm, the incidence of PHN may not be significantly influenced by the absence of placebo. Even so, randomized, blinded, placebo-controlled clinical trials are needed. The study period in this trial is limited to 12 weeks; consequently, little is revealed about the long-term preventive effectiveness of duloxetine. Similarly, the maximum dosage of duloxetine was set at 60 mg per day, and this study does not address whether a higher dosage would have a more significant advantage or what dosage is optimal in the prevention of PHN. For safety reasons, immunosuppressed patients will not be included in the current study. Further investigation is needed for that population.

## Trial status

This protocol version 1.1 (2020/04/10) has been approve by the IRB of Beijing Tiantan Hospital Affiliated to Capital Medical University. We plan to begin trial recruitment on August 1, 2020. We estimate that the study will need to continue for 3 years to reach the intended goal of 750 participants. Hence, recruitment for this PROCESS trial is expected to complete by September 30, 2023.

## Abbreviations

PHN: Postherpetic neuralgia
HZ: Herpes zoster
VZV: Varicella zoster virus
TCA: Tricyclic antidepressants
VAS: Visual analogue scale
PD: Pain diary
AE: Adverse events
SAE: Serious adverse events
SF-12: Short-Form Health Survey
PGIC: Patient Global Impression of Change Scale
PSQI: Pittsburgh Sleep Quality Index
DSMB: Data Safety Monitoring Board
WHO: World Health Organization
QoL: Quality of life
IRB: Institutional Review Board
CC: Coordinating centre
PI: Principal Investigator
TSC: Trial steering committee
DMC: Data monitoring committee
NE: Norepinephrine
